### Sample size

The sample size was calculated based on previous studies. Earlier findings showed a reduction in hamstring injury incidence of up to 70% with eccentric training of the hamstring muscle, an injury incidence of 1 in 11 players per soccer season, and recurrence rates of 12–30% [16, 17]. On the basis of these findings and two-sided testing, significance level of 0.05, power 0.8, an inflation correction for cluster randomization of 1.19, drop-out of 20%, and loss to follow-up of 20%, we calculated that 26 teams of approximately 16 players would have to be included. Taking into account that the follow-up period is in a new soccer competition, with a larger loss to follow-up, we included 10% extra players, so that in total the study includes 30 teams with about 16 players/team (*n* = 480).

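### The 26 teams stated for 80% power do not follow from the listed inputs; for the 30 teams included, power is about 0.59 to 0.69 on a two-proportion test with the stated losses

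*Protocol article*

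**What the plan says.** All of this is in the protocol article, Methods/design, Sample size. The calculation is said to rest on "a reduction in hamstring injury incidence of up to 70" per cent with eccentric training, "an injury incidence of 1 in 11 players per soccer season" and "recurrence rates of 12–30" per cent. To these it adds "two-sided testing, significance level of 0.05", power 0.8, and "an inflation correction for cluster randomization of 1.19, drop-out of 20%, and loss to follow-up of 20" per cent. The result is "we calculated that 26 teams of approximately 16 players would have to be included", which is 26 × 16 = 416 players. A further 10% is then added because more loss is expected in the follow-up that falls in the next season's competition, so that "in total the study includes 30 teams with about 16 players/team" (n = 480).

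Recruitment of participants and randomization gives equal numbers of teams per arm. Statistical methods lists chi-square, Poisson and Cox analyses for the primary outcomes. The formula behind the 26 teams is not given. Nor is it said how the two 20% allowances combine or what part the recurrence rates play.

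**The concern.** Inputs and result are printed together, so the result can be checked, and it fails the check. The 416 players are fewer than a plain two-proportion comparison needs before clustering or attrition is allowed for, although the text says that both were.

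Hamstring injury incidence is a primary outcome, and 0.8 is the only power figure given. If the real figure is nearer 0.6 or 0.7, a non-significant result is considerably more likely than the stated 20%, even if the programme works as well as the best result cited. A reader relying on the 0.8 would then take such a result as stronger evidence against the programme than it is. The effect size leaves no slack, because 70% is the top of the cited range (the Background gives 66–70%).

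**Working it through.** **Inputs (Sample size section).** Control risk p1 = 1/11 = 0.0909. Intervention risk p2 = 0.3 × p1 = 0.0273. Two-sided 0.05 (z = 1.960), power 0.80 (z = 0.842). Design effect 1.19. Two allowances of 20%. Sixteen players per team, 1:1 allocation.

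**Attempt to reproduce 416 players, two proportions.** Unpooled variance:

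n per arm = (1.960 + 0.842)² × [p1(1−p1) + p2(1−p2)] / (p1−p2)² = 7.849 × (0.0826 + 0.0265) / 0.0636² = 211.6.

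The pooled-variance form gives 214.3. In total:

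| Step | Players | Teams of 16 |
|---|---|---|
| No inflation | 423–429 | 26.4–26.8 |
| × 1.19 | 504–510 | 31.5–31.9 |
| and one 20% loss (/0.8) | 630–638 | 39.3–39.9 |
| and both losses added (× 1.4) | 705–714 | 44.1–44.6 |
| and both losses multiplied (/0.64) | 787–797 | 49.2–49.8 |

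The stated 26 teams agree only with the first line, which has no inflation.

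**Log-rank alternative (a Cox analysis is also planned).** Events needed = 4 × 7.849 / (ln 0.3)² = 21.7. The mean risk over both arms is (0.0909 + 0.0273)/2 = 0.0591, so 21.7/0.0591 gives about 367 players. With 1.19 this is 436 (27.3 teams); with one loss, 545 (34.1); with both added, 611 (38.2); with both multiplied, 682 (42.6).

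**Recurrences as extra independent events.** Raising the event rate by 30%, the top of the listed range, lowers the log-rank base to 282 players. With 1.19 and one loss: 282 × 1.19 / 0.8 = 419 (26.2 teams). With both losses added: 470 (29.4 teams). With both multiplied: 524 (32.8 teams).

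**Power with the 30 teams included.** For two proportions the effective number per arm is 480 × retention / (2 × 1.19), and power = Φ{(p1−p2)/√[(p1(1−p1)+p2(1−p2))/n] − 1.96}. For log-rank, power = Φ{½√d × |ln 0.3| − 1.96}, where d = 0.0591 × 480 × retention / 1.19.

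| Retention | Effective n per arm | Two proportions | Log-rank |
|---|---|---|---|
| 1.00 | 201.7 | 0.78 | 0.84 |
| 0.80 (one loss) | 161.3 | 0.69 | 0.75 |
| 0.64 (both, multiplied) | 129.1 | 0.59 | 0.65 |

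The pooled form lowers the two-proportion values by less than 0.01. With 30% recurrences as extra events and both losses, log-rank power is 0.76 (multiplied) or 0.81 (added). For the 26 teams to which the 0.8 is attached, two-proportion power is 0.72, 0.62 and 0.53 for the same three retentions.

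**Detectable reduction at 80% power, 30 teams, two proportions (unpooled).** About 71% with no attrition, 78% with one loss and 84% with both multiplied. If the true reduction were 66%, power with both losses would be 0.53.

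**The case against.** The strongest reply is that the text does not fix the method, and that some readings are kinder.

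- **The second loss.** The article places its follow-up period in a new competition, which is where long-term compliance is measured. The 20% loss to follow-up may therefore not bear fully on an injury outcome collected during the season. This stands as an open question. With one loss only, the two-proportion need is 39 to 40 teams and power is 0.69.
- **Partial follow-up.** Exposure and injuries are reported weekly, and Poisson and Cox analyses are planned, so players who leave still contribute time until then. Treating them as contributing nothing overstates the loss. This also stands.
- **Recurrences.** They are listed among the findings on which the calculation rests. Log-rank with 30% recurrences and one loss comes to 26.2 teams, and with both losses added to 29.4. The first omits one stated allowance, and the second supports 30 teams, not 26. Both treat a player's repeat injuries as independent of his first, which is optimistic.

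For these reasons some stronger conclusions are not supported. A reader might infer that the trial needs 49 to 50 teams and that its real power is 59%. Both figures hold only for a two-proportion test with the losses multiplied and recurrences ignored. A reader might also infer that 30 teams fall short of 80% power even without attrition. That is true for two proportions (0.78) but not for log-rank (0.84). Nor can it be said that the inflation was simply forgotten. Among other explanations, a per-arm figure may have been used as the total (215 × 1.19 / 0.6 = 426 players, 26.7 teams per arm), and the article does not allow a choice between them.

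**Conclusion.** The point holds: 26 teams at 80% power is not a consequence of the inputs printed beside it. No two-sided reading was found that applies 1.19 and both 20% losses in full and gives 26 teams. This does not depend on the choice between pooled and unpooled variance, on a two-proportion or log-rank formula, or on whether the losses are added or multiplied.

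The size of the shortfall does depend on choices that the article leaves open. At a 70% reduction, power for the 30 teams is about 0.59 to 0.69 for a two-proportion comparison with both losses or one, and 0.65 to 0.75 for log-rank. It reaches 0.76 to 0.81 with both losses only if up to 30% recurrences count as extra independent events. All these figures use the article's own 1.19 and its most favourable effect.

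That a journal article condenses a fuller protocol does not remove the problem. The complaint is that the printed inputs and the printed result disagree, not that detail is absent.

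**What to change.** Keep the 30 teams and correct the Sample size paragraph. It should state:

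1. the formula used;
2. whether the two 20% losses add, compound, or in the second case apply only to the new-season follow-up;
3. how the recurrence rates enter, if at all;
4. the resulting power for 30 teams of 16 with design effect 1.19, in place of the unqualified 0.8. For a two-proportion comparison this is about 0.69 with one loss and 0.59 with both multiplied;
5. the reduction detectable with 80% power, about 84% with both losses and 78% with one.

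If another method or other inputs produced the 26 teams, stating them so that the figure can be reproduced would also resolve the point. The cost is one rewritten paragraph and a less favourable stated power. Recruitment, conduct and data collection do not change.

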### Statistical methods

SPSS version 22 will be used to analyse the data. Descriptive statistics will be used to analyse the baseline characteristics. The incidence of hamstring injuries will be analysed on an intention-to-treat basis. The primary outcomes will be compared in the intervention and control groups using Chi square tests, Poisson general log-linear analysis, and Cox regression analysis with survival curves.

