### Recruitment of participants and randomization

Dutch male soccer players (age 18–40 years) playing in the Dutch first-class amateur competition were eligible for participation. All players were asked to give their written informed consent before the start of the study. Players who did not give their informed consent, who joined a team after the start of the study, or who had a lower than average understanding of Dutch were excluded.

After selection of the four districts, a top-down strategy was carried out to recruit the soccer teams. First, the boards of the clubs were informed about the study by means of an email from the director of amateur soccer of the KNVB and the research team. Then the members of the medical staff and the coaches were invited, by telephone, to attend a meeting to tell them about the purpose and methods of this study. If the clubs decided to participate in this study, all players of the participating teams received an information letter including an informed consent form. To avoid a risk of contamination, the teams were randomized as clusters instead of individual players [37]. Randomization was done independently by an online randomizer (https://www.randomizer.org/) and an equal number of teams were assigned to the intervention and control groups. After randomization, meetings were organized in each district to inform staff and players in the intervention group about the BEP.

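### Teams were randomized, but the three planned tests treat players as independent, so intervals are too narrow and the false-positive rate exceeds 5% (about 7% on the plan's own figure)

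*Protocol article*

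**What the plan says.** Three sections of the protocol article bear on this point.

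- **Recruitment of participants and randomization:** to limit contamination, "the teams were randomized as clusters instead of individual players", and "an equal number of teams were assigned to the intervention and control groups". With the 30 teams given under Sample size, that is 15 teams per arm.
- **Sample size:** the calculation rests on "two-sided testing, significance level of 0.05, power 0.8, an inflation correction for cluster randomization of 1.19", with about 16 players per team.
- **Statistical methods:** incidence is analysed by intention to treat, and the primary outcomes are to be "compared in the intervention and control groups using Chi square tests, Poisson general log-linear analysis, and Cox regression analysis with survival curves".

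The article nowhere mentions a team effect, generalized estimating equations (GEE), cluster-robust standard errors, shared frailty or an analysis of team summaries.

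**The concern.** The design treats players in one team as correlated and pays for this with extra players. The analysis section then names three methods which, in their ordinary form, take each player as an independent observation. The two parts of the plan rest on different assumptions about the same data.

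Players in a team share a coach, medical staff and training load, so some correlation of injuries within teams is plausible. If it is present, the effective sample is smaller than the number of players. A player-level standard error for the intervention effect is then too small, intervals are too narrow, and a difference is declared too often when there is none. The fault touches every method named for the primary outcomes, and it always works towards finding a difference.

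**Working it through.** **Inputs**

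| Input | Value | Source |
|---|---|---|
| Unit and allocation | team, equal numbers per arm: 15 v 15 | Recruitment and randomization; Sample size |
| Players per team, m | about 16 | Sample size |
| Design effect, DE | 1.19 | Sample size |
| Test | two-sided, 5% | Sample size |
| Injury risk | 1/11 = 0.0909 per season | Sample size |
| Attrition | 20% drop-out and 20% loss to follow-up | Sample size |
| Intracluster correlation (ICC) | not given | derived below |

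**Step 1: what 1.19 implies.** The article gives no ICC, so 1.19 cannot be rebuilt from its parts, only solved backwards. With equal teams, DE = 1 + (m − 1) × ICC, so ICC = 0.19/15 = 0.0127.

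The stated 26 teams (26 × 16 = 416 players) could not be reproduced either. For a 70% reduction from 1/11 with 80% power, the pooled two-proportion formula gives 215 per arm, 430 in all. Then 430 × 1.19 is about 512, and 512/(0.8 × 0.8) is about 800 players, or 50 teams. That is a separate question, and nothing below uses the 26.

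**Step 2: standard error and interval width.** A player-level analysis omits the factor √DE = √1.19 = 1.091. Its intervals have 1/1.091 = 0.917 of the proper width, so they are 8.3% too narrow.

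**Step 3: true error rate.** 2 × [1 − Φ(1.96/√1.19)] = 2 × [1 − Φ(1.797)] = 0.0724. A nominal 5% test has a true error rate of 7.2%, and a nominal 95% interval covers 92.8%.

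**Step 4: simulation.** Beta-binomial data were generated with no intervention effect: 15 v 15 teams of 16, risk 1/11, 100,000 runs.

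| ICC | Player-level chi-square rejects | Team-level t-test rejects |
|---|---|---|
| 0 | 4.9% | 5.0% |
| 0.0127 | 7.0% | 4.9% |
| 0.03 | 10.3% | 4.9% |
| 0.05 | 13.4% | 4.8% |

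The excess comes from clustering alone: it is absent at ICC 0, and an analysis at team level removes it.

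**Step 5: sensitivity, using the formulas of steps 2 and 3.** ICC values other than 0.0127 are assumptions.

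| Players per team | ICC | DE | True error of a 5% test | Interval width ratio |
|---|---|---|---|---|
| 16 | 0 | 1.000 | 5.0% | 1.000 |
| 16 | 0.005 | 1.075 | 5.9% | 0.964 |
| 16 | 0.0127 | 1.190 | 7.2% | 0.917 |
| 16 | 0.02 | 1.300 | 8.6% | 0.877 |
| 16 | 0.03 | 1.450 | 10.4% | 0.830 |
| 16 | 0.05 | 1.750 | 13.8% | 0.756 |
| 12.8 (one 20% loss) | 0.0127 | 1.149 | 6.8% | 0.933 |
| 10.24 (0.8 × 0.8 × 16) | 0.0127 | 1.117 | 6.4% | 0.946 |

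**The case against.** **The article is silent; it does not state an independence assumption.** The section is a few sentences that name families of methods. Poisson and Cox models can both carry a team effect or a robust variance, a chi-square statistic can be divided by a design effect, and a fuller protocol or analysis plan may say so. This is the strongest point. Such a plan may exist, and if it handles teams properly the two documents need only be reconciled. But the article does more than leave detail out: it commits the primary comparison to three named methods. An ordinary chi-square test on players has no place for a team term, so further detail cannot make it valid here; an adjusted version would be a different test, which the text does not name.

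**The size depends on an ICC that the article never states.** This stands. The 7.2% holds if the ICC in the trial matches the one implied by 1.19 with equal teams of 16. It falls to about 6.4% if both attrition allowances remove players, to 5.9% at ICC 0.005, and to 5% at ICC 0. The direction is the same for any positive ICC, and a design effect above 1 is the plan's own assumption.

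**Only the chi-square test was simulated.** This also stands. The Poisson and Cox analyses were not simulated, and severity, the other primary outcome, was not examined. The formula in step 3 covers any player-level estimate whose variance is understated by the design effect, but the design effect for rates, times or days lost may differ from 1.19.

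**The mechanism is inferred.** The article's stated reason for cluster allocation is contamination. The shared-environment argument is the reviewer's, although the 1.19 shows that some variance inflation was expected.

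**Conclusion.** The point holds and must be fixed. Teams were randomized and the sample size allows for this, but the analysis as written does not. Under the plan's own design effect of 1.19, the false-positive rate is 7.2% instead of 5% and intervals are 8.3% too narrow.

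That is a moderate inflation, and it is somewhat smaller (about 6.4%) if teams shrink to around 10 players. It grows quickly if the ICC is larger than the plan supposes. The figures assume equal team sizes, a positive ICC and the ordinary form of the three tests. Severity calls for correction as well as size, because an analysis that ignores the randomized unit is not a valid test of the primary question in a cluster trial.

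**What to change.** Amend the Statistical methods section as follows.

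1. Name one primary analysis of incidence: a Poisson (or negative binomial) model for the number of hamstring injuries, with log exposure hours as offset and team as the cluster, either as a random intercept or as the subject in GEE.
2. Add a correction for the small number of clusters: a t reference with about 28 degrees of freedom (30 teams minus 2), or a bias-corrected robust variance.
3. Give the Cox model a team frailty or a cluster-robust variance.
4. Replace the player-level chi-square test by a comparison of team-level rates or proportions.
5. Report the estimated ICC.

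If a separate analysis plan already does this, bring the two texts into line.

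**Cost.** Team membership is already known, so no new data are needed. Under 1.19 the intervals widen by a factor of about 1.091 for clustering. A t reference with 28 degrees of freedom adds 2.048/1.960 = 1.045, so intervals are about 1.091 × 1.045 = 1.14 times as wide as the unadjusted ones. The clustering part is what the 1.19 was meant to pay for.

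The article fixes SPSS version 22. Random-intercept and GEE count models should be within its mixed and GEE procedures. Support for a Cox frailty, a cluster-robust Cox variance or the bias-corrected variance should be checked, and other software named if needed. The team-level comparison needs no special software.

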### Ethical approval

This trial was approved by the Medical Ethics committee of University Medical Centre of Utrecht (16–332\C) and is registered in the Dutch trial register (http://www.trialregister.nl/trialreg/index.asp) (NTR6129). All participants received a written information letter, and any questions were answered (verbally or in writing) by one of the researchers ([name]). All participants were asked for their informed consent, and all data are handled according to legal requirements.

## Discussion

Hamstring injuries are a major problem in amateur soccer players. Recent studies have shown that a reduction in hamstring injury incidence up to 70% can be achieved by eccentric training following the NHE programme [16, 17]. While NHE compliance was high in studies, the NHE programme has not been adopted in amateur soccer and the number of hamstring injuries has not diminished yet [17, 18]. Arguments for non-compliance are lack of time, delayed onset muscle soreness, the need to sit on the ground or a mat, and not sport- specific enough to incorporate into the warming-up [19, 20].

The BEP, consisting of a gradual build-up to plyometric (bounding) exercises, is a more sport-specific injury prevention programme, so that compliance is expected to be better. It can be easily implemented during warming-and is expected to improve sprint and jumping performance [29–32].

This study has the advantage of a standardized methodology and consensus regarding definitions of injuries and exposure [44]. The self-reported registration via modern systems, such as SMS and NetQ, will probably ensure valid injury registration and optimal compliance.

## Abbreviations

BEP: Bounding Exercise Programma
HIPS-3: Hamstring Injury Prevention Study-3
KNVB: Royal Netherlands Football Association
NHE: Nordic Hamstring Exercise
SPIRIT: Standard Protocol Items Recommendations For Interventional Trials
